**Figure 2 figure2:**
[figure not shown]
Design of the MARCHE clinical trial.

### Study Treatment Groups

The study consists of 2 treatment groups, both of which will include the wearable activity monitor. Participants in group A will receive the OA GO mobile app, and their wearable activity monitors will be unblinded. They will be able to view the data from their monitors on an ongoing basis. The OA GO mobile app, which will be downloaded to an iPhone (provided by the study sponsor), contains motivational messages and requests that the patients enter their pain and mood on a daily basis. Training on the use of the mobile app will be provided by the study site. The OA GO app will obtain information from the wearable activity monitor and combine the data with data entered by the patient (such as daily pain and mood). In group B (the control arm of the study), the wearable activity monitors will be blinded; that is, patients in group B (who are blinded to their wearable activity monitor) will not have any access to data recorded by the wearable activity monitor. Data will be downloaded by the study team at last visit. Patients in both treatment groups will receive regular follow-up per the standard-of-care information regarding the benefits of walking from the Arthritis Foundation [13].

## Results

### Study Outcomes

The primary study endpoint is the difference in the change in mobility (assessed by steps per day) between groups at the end of 90 days. Baseline steps per day will be the average of the steps recorded on the wearable activity monitor over 7 days during screening, and the final-visit steps per day will be the average of the steps recorded on the wearable activity monitor over the last 7 days for which steps are recorded. Secondary efficacy endpoints include physical function, assessed by the change from baseline in the 6-minute walk test (distance and pain (pain assessed on an 11-point numeric rating scale, ranging from 0-10)), and percent change from baseline in steps per day. The 6-minute walk test is a validated measure sensitive to assessing changes in the physical performance of older adults [50,51], and has been found to be a reliable measure of functional performance in patients following total hip and total knee arthroplasty [52,53].

Patient-reported outcomes include patient and physician satisfaction with treatment (measured by 6 items for each, on a 7-point Likert scale, and a final item assessing likelihood of using the device in the future (patient) and recommending the device (physician)), PAM-13 scores (responses on a Guttman-like scale ranging from 1-4 (strongly disagree to strongly agree), resulting in possible scores from 13-52 and converted to activation scores ranging from 0-100, the highest degree of activation), and patient-entered values for daily pain and mood for those in the mobile OA GO group. The PAM-13 [54,55] is a reliable and valid measure of patient activation, with higher scores associated with increased self-management behaviors, increased self-efficacy, and activation making it useful for evaluating interventions in a clinical setting.

Tertiary endpoints include target knee pain with walking and at rest, as measured by the 11-point numeric rating scale at final visit; mood at final visit (as measured by the VAMS (capturing 8 domains of mood with raw scores transformed into T-scores with a mean of 50 and standard deviation of 10)); pain and mood as entered into the OA GO app by patients in the mobile OA GO group; sleep quality as measured by the wearable activity monitor; and change from baseline in weight. The VAMS is a brief measure of internal mood state validated in both normal and neurologically impaired individuals [56,57]. Analysis of the relationships between activity and pain, activity and mood, and sleep will also be performed. Lastly, adherence to the use of the mobile OA GO app plus the wearable activity monitor over 90 days after completion of the trial (in patients who received the mobile app) will be determined. Adverse events, including device-related complaints, will also be assessed.

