Figure 2 shows the study protocol. Patients who are selected by the investigator for treatment with hylan G-F 20 for OA of the knee will be screened for eligibility, and their baseline pain will be assessed. Patients will also be required to provide written informed consent. If eligible, patients will be given a wearable activity monitor (Jawbone UP24) that will record their daily steps and other variables over the next 7 days (to establish their baseline activity level). Jawbone UP24 is a commercially available wearable activity monitor designed to be worn on the wrist. After at least 7 days, patients will return for assessment of baseline activity, mood (using Visual Analog Mood Scales (VAMS) [49]), and a baseline 6-minute walk test. Eligible patients will receive a single intra-articular injection of hylan G-F 20 in the knee and will be randomized to receive either the mobile OA GO app (unblinded and able to view data from their wearable activity monitor on an ongoing basis) or standard-of-care instructions (blinded with no access to activity recorded by the wearable monitor); randomization will be stratified by site. Additional study visits are performed at days 7 and 30, with the final visit at day 90, when the last evaluation of the primary endpoint will be performed, along with assessments of pain, 6-minute walk test, mood (VAMS), PAM-13, and patient/physician satisfaction. At the end of the trial, all data from the mobile OA GO app will be downloaded and patient adherence will be checked.

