### Data Analysis

The target sample size in this study is 200 participants, which assumes an attrition rate of 15%. Based on a two-sided significance level of 5%, the study will have 80% power to detect an average increase of 25% in the change from baseline in steps per day for those in the unblinded wearable activity monitor group using the OA GO mobile app, compared with those in the blinded wearable activity monitor group who did not have the mobile app.

Efficacy outcomes will be analyzed in the modified intent-to-treat population (all randomized patients with baseline and on-treatment values for the primary endpoint from day 30 onward). Analysis of covariance with baseline mean steps per day as covariate and treatment and pooled site as class variables will be used to compare between-group outcomes. Satisfaction surveys at last visit will be summarized. Safety outcomes will be analyzed for all patients provided a wearable activity monitor.

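### The primary endpoint is set at 90 days, but its final value may come from any time after about day 30, so early stoppers are in effect carried forward to day 90

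*Protocol article*

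**What the plan says.** Under Study Outcomes, the primary endpoint is "the difference in the change in mobility (assessed by steps per day) between groups at the end of 90 days". Under Patient Eligibility Criteria and Study Design, follow-up closes "with the final visit at day 90, when the last evaluation of the primary endpoint will be performed".

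Study Outcomes then defines the two values that enter the change. For the first: "Baseline steps per day will be the average of the steps recorded on the wearable activity monitor over 7 days during screening". The second, labelled as the final-visit value, is the average of "the steps recorded on the wearable activity monitor over the last 7 days for which steps are recorded". No study day is attached to that window.

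Under Data Analysis, the efficacy population is "all randomized patients with baseline and on-treatment values for the primary endpoint from day 30 onward". The model is an analysis of covariance with baseline mean steps, treatment and pooled site. It has no term for when the final value was recorded.

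Under Study Treatment Groups, the arms differ in what patients see. Of the app group the article says "They will be able to view the data from their monitors on an ongoing basis", and the app also sends motivational messages. The control group has no access to its monitor data.

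**The concern.** The time point in the endpoint and the time point of the measurement are two different things. A patient whose recording ends in the fifth week enters the primary analysis with a fifth-week value standing for day 90. This assumes that steps stay flat after recording stops. Both the response to the injection and engagement with a new app could change over three months, so the assumption is not a safe default.

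Timing can also differ by arm. One arm gets continuous feedback and messages, while the other wears a monitor that shows it nothing, so the incentive to keep recording differs by design. If recording time depends on treatment, randomisation no longer guarantees that the arms are compared at the same time since injection. What is at stake is whether the headline difference in steps per day estimates the 90-day effect that the article announces.

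**Working it through.** **1. How early can the final value be?** The only limit is the day-30 condition in the efficacy population.
- If the last recorded day may be day 30, the gap is 90 − 30 = 60 days.
- If all seven days must fall on or after day 30, the earliest window is days 30 to 36, and the gap is 90 − 36 = 54 days.

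Either way the value can be roughly two months early. For a patient still recording at day 90, the gap is zero and the two definitions give the same number.

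**2. A scale for the illustration.** Data Analysis gives 200 participants, 15% attrition, two-sided 5% and 80% power. It gives no SD and no absolute difference in steps, so 200 cannot be reproduced from its own inputs. It can only be solved backwards:
- evaluable: 200 × 0.85 = 170, or 85 per arm;
- standard error of a difference in SD units: √(2/85) = 0.153;
- implied effect: (1.960 + 0.842) × 0.153 = 0.43 SD.

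As a consistency check, 0.43 SD needs 85 per arm, and 170 / 0.85 = 200.

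**3. Bias formulas.** Suppose early stoppers contribute day-30 values and everyone else day-90 values, and stoppers are otherwise like the rest.
- Changing effect, same share s carried forward in both arms, no other trend: expected estimate = (1 − s) × (day-90 effect) + s × (day-30 effect).
- Common trend g between day 30 and day 90, no treatment effect, shares sA (app) and sB (control): bias = g × (sB − sA).
- Rejection rate for a shift b: 1 − Φ(1.960 − b/0.153) + Φ(−1.960 − b/0.153).

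**4. Results.** The shares, day-30 effects and trends are assumptions. None of them is in the article.

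| Scenario | Share carried forward | Result |
|---|---|---|
| (a) 0.43 SD at day 30, zero at day 90 | 5% | shift 0.021 SD, rejection rate 5.2% |
| | 15% | shift 0.064 SD, rejection rate 7.0% |
| | 25% | shift 0.107 SD, rejection rate 10.8% |
| (b) 0.43 SD at day 90, half of it at day 30 | 5% | power 78.0% instead of 80% |
| | 15% | power 73.6% |
| | 25% | power 68.8% |
| (c) no effect, common trend 0.5 SD | 15% in each arm | no bias, rejection rate 5% |
| | 5% app, 25% control | bias 0.10 SD, rejection rate 10.0% |
| (d) constant effect, no trend | any | no bias |

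Worked line for (a) at 15%: b = 0.15 × 0.43 = 0.064; b/0.153 = 0.42; 1 − Φ(1.54) + Φ(−2.38) = 0.062 + 0.009 = 0.070.

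In (c), with the same 5% versus 25% split, trends of 0.25 SD and 1 SD give rejection rates of 6.2% and 25.6%.

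(a) favours the app and (b) works against it. In (c) the sign depends on the direction of the trend and on which arm stops earlier.

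**The case against.** The strongest reply is that few patients may be affected. The final visit is at day 90, and for anyone recording until then the rule gives a day-90 value. The only related figure, 15% attrition, can include losses before day 30, which the population rule excludes. This stands, and it is why no size can be claimed.

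Three stronger readings are tempting, and the article supports none of them.
- A reader might infer that the reported result would not be a 90-day effect at all. That goes too far, because only patients who stop between about day 30 and day 90 are displaced.
- A reader might infer that the rule must flatter the app, because early stoppers would keep a novelty peak. That needs a fading effect, for which the article gives no evidence. If the effect builds up instead, the bias runs the other way.
- A reader might infer that a single recorded day after day 30 qualifies a patient, with the other six days taken from before. The condition "on-treatment values for the primary endpoint from day 30 onward" can equally mean that the whole seven-day mean lies after day 30. The text does not settle this.

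It can also be said that minimum valid days, consecutive-day rules and missing-data models belong in an analysis plan that is not shown. Their absence is indeed no finding. The window itself is different: the article states it, and a calendar window at day 90 would contradict that rule, not add detail to it.

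Finally, a repeated-measures model or multiple imputation does not remove the problem if patients stop because they have disengaged. That stands and is carried into the fix.

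**Conclusion.** The point holds in a limited form. The stated endpoint is at 90 days. The stated final value is not tied to day 90 and can be up to about 60 days early for patients who stop recording after day 30. Nothing in the article limits the window or adjusts for its timing. For those patients the rule is last observation carried forward in effect, although the article does not use the term.

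The estimate is biased for day 90 under either of two conditions: the app effect changes after day 30, or steps trend over time and early stopping differs by arm. If neither holds, there is no bias. Size and direction are unknown. The rates of about 7% (15% carried forward) and about 10% (0.5 SD trend, 5% versus 25% stopping) show what is possible under assumed inputs. They do not predict what will happen in this trial. The point is worth correcting because it concerns the primary endpoint and the repair uses data that the monitors already record.

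**What to change.** Make the change before any data are analysed, with a dated record, since the Discussion says enrollment is complete and the trial is open-label.

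1. Define the final value as the mean steps per day over a fixed window ending at the day-90 visit, for example seven days, with a stated minimum number of valid days.
2. Treat patients without a value in that window as missing at day 90.
3. Estimate the day-90 difference with a repeated-measures model on weekly means, or with multiple imputation. Keep baseline steps, treatment and pooled site in the model.
4. Include all randomised patients with a baseline and any post-baseline step data, so that the day-30 condition no longer selects the population. Without this step, part of the selection would remain.
5. Keep the analysis of covariance on the last seven recorded days as a sensitivity analysis.
6. Tabulate the study day of the last recorded steps by arm, so that readers can see how much depends on early stopping.

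The cost is a revised endpoint and analysis text and probably a slightly larger standard error. No new patients or measurements are needed. The new analysis relies on data being missing at random, which is doubtful if stopping reflects disengagement. A sensitivity analysis should therefore let the unrecorded weeks differ from the recorded ones by a range of assumed amounts.

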### Data Analysis

The target sample size in this study is 200 participants, which assumes an attrition rate of 15%. Based on a two-sided significance level of 5%, the study will have 80% power to detect an average increase of 25% in the change from baseline in steps per day for those in the unblinded wearable activity monitor group using the OA GO mobile app, compared with those in the blinded wearable activity monitor group who did not have the mobile app.

Efficacy outcomes will be analyzed in the modified intent-to-treat population (all randomized patients with baseline and on-treatment values for the primary endpoint from day 30 onward). Analysis of covariance with baseline mean steps per day as covariate and treatment and pooled site as class variables will be used to compare between-group outcomes. Satisfaction surveys at last visit will be summarized. Safety outcomes will be analyzed for all patients provided a wearable activity monitor.

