## Methods

### Patient Eligibility Criteria and Study Design

Patient inclusion and exclusion criteria are listed in Textboxe 1 and Textboxe 2. The inclusion criteria were designed to identify patients who were candidates for treatment with hylan G-F 20 and would be capable of using the wearable activity monitor and a smartphone.

The MARCHE study is a randomized (1:1), open-label, multicenter, parallel-group study in patients with OA of the knee treated with hylan G-F 20. The trial will be conducted in accordance with the Declaration of Helsinki and the International Conference on Harmonisation Guideline for Good Clinical Practice, and each investigator will obtain institutional review board or ethics committee approval. The primary objective of the study is to demonstrate the impact of a mobile app (OA GO) plus a wearable activity monitor in increasing the mobility of patients with knee OA who were treated with hylan G-F 20. Secondary objectives include evaluating the impact of the OA GO app combined with the wearable activity monitor on a 6-minute walk test, assessing patient and physician satisfaction with the OA GO app and the wearable activity monitor, determining the percent change from baseline in steps per day, and determining between-group changes from baseline in the Patient Activation Measure-13 (PAM-13), which assesses patient activation regarding health self-management. Relationships among mobility, pain, mood, and sleep will also be established.

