## Discussion

### Summary and Limitations

Adoption of mHealth technologies into the management of knee OA and other chronic diseases that rely on self-management has the potential to improve patient outcomes; however, data to support this potential are needed. The approach of using these new technologies will also need to be validated. As a first step, the MARCHE study evaluates the impact of a mobile app, combined with a wearable activity monitor, on mobility in patients with knee OA treated with hylan G-F 20. The first patient was enrolled in August 2014, and study enrollment has since been completed.

One limitation of the study is that the investigators are not blinded to the intervention, which could bias the delivery of other aspects of care to the patient. In addition, the step count is only an estimate of the patients’ mobility and is specific to the Jawbone device, so it may not be representative of all devices. The study was focused on activity monitoring and could have included an evaluation of WOMAC scores to assess patient subjective evaluation of changes in condition and function. Finally, the 6-minute walk test could be considered less representative of real-life mobility compared with 6 minutes of walking taken at different time intervals. Future studies could use “continuous walk tests” over a 24-hour period, an example of which would include both a 6-minute walk test and a 25-foot walk test that could be continuously run with algorithms in place to discard, for example, periods of rest, sleep, and driving.

The field of mHealth will continue to evolve. In particular, wearable devices may eventually become implantable devices, which are increasingly being used for health purposes.In 2004, the US Food and Drug Administration approved radio frequency identification tags for human implants, although some safety concerns are associated with these tags. They are small, which means they can move under the skin and become difficult to remove. Internally powered tags could also cause electromagnetic interference with medical devices such as defibrillators. Implantable sensors are currently in development for monitoring glucose and free-floating proteins as biomarkers.

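### The efficacy population depends on step recording from day 30 onward, a post-randomisation filter that may act differently in the two arms

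*Protocol article*

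**What the plan says.** All references are to the protocol article.

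- **Population.** Data Analysis states: "Efficacy outcomes will be analyzed in the modified intent-to-treat population". It defines that set as "all randomized patients with baseline and on-treatment values for the primary endpoint from day 30 onward". The article names no other efficacy population.
- **Endpoint.** Study Outcomes defines the primary endpoint as the "difference in the change in mobility (assessed by steps per day) between groups at the end of 90 days". The final value is "the average of the steps recorded on the wearable activity monitor over the last 7 days for which steps are recorded". The 6-minute walk test (distance and pain) is listed there as a secondary efficacy endpoint.
- **Design.** Patient Eligibility Criteria and Study Design describes a "randomized (1:1), open-label, multicenter, parallel-group study". The 7-day baseline recording comes before the visit at which patients are injected and randomised, and the exclusion criteria set limits on baseline daily steps.
- **Arms.** Under Study Treatment Groups, both arms wear the monitor. App patients see their data, get motivational messages and are asked for daily entries. Control patients "will not have any access to data recorded by the wearable activity monitor".
- **Size.** Data Analysis sets a target of 200 patients with 15% attrition, 80% power and a two-sided 5% level.

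**The concern.** Every patient needs a baseline step average to be found eligible, so the baseline half of the definition removes almost nobody. The half that removes patients is the need for step values from day 30 onward. That condition is met or failed after randomisation, and the assigned arm could influence it: one arm has feedback and prompts to keep using the device, and the other wears a band that shows it nothing.

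The route by which data are collected may add to this. The text on the control arm says that data are downloaded at the last visit, while the app takes in monitor data as part of its use. If that difference is real, a control patient who never returns could have no step data, while an app patient leaving at the same time could already have some.

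If the patients removed differ between arms in number or in kind, the groups analysed are no longer the groups that were randomised. Baseline-adjusted analysis of covariance repairs this only if baseline steps, arm and site explain who is missing. The same filter governs the 6-minute walk test, so a patient who completed that test but lacks step data is left out of an analysis to which the patient could contribute.

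**Working it through.** **1. The plan's own figure.** The stated total is 200. The article gives no SD, so this total cannot be reproduced independently; that is not treated as an error here. Working backwards:

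- Evaluable patients: 200 × (1 − 0.15) = 170, or 85 per arm.
- Implied standardised difference, normal approximation: (1.960 + 0.842) × √(2/85) = 0.430 SD. The t-based value is 0.432.
- If the 25% increase is read as 25 percentage points, the implied SD is 25 / 0.430 ≈ 58 points. With an SD of 58, the formula returns 85 per arm and 170 / 0.85 = 200, so the total is feasible.

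The yardstick below is 0.43 SD.

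**2. How many patients could be removed.** At 15% attrition, 0.15 × 200 = 30 patients leave. That is the upper limit at the planned rate, reached only if all of them stop recording before day 30. Patients who stop later remain in the set, because their final value comes from their last 7 recorded days.

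**3. Bias formula.** In one arm, let *m* be the share excluded and *D* the mean of retained minus the mean of excluded patients, in SDs. The whole-arm mean is (1 − m) × retained + m × excluded, so the retained mean exceeds it by m × D. The between-arm bias is

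m(app) × D(app) − m(control) × D(control).

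**4. Equal exclusion.** With the same *m* and *D* in both arms, for example 15% in each, the bias is 0 and the type I error stays at 5.0%.

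**5. Exclusion in one arm only (assumed inputs).**

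| Share excluded | D (SD) | Bias (SD) | Share of 0.43 |
|---|---|---|---|
| 10% | 0.5 | 0.10 × 0.5 = 0.050 | 12% |
| 15% | 0.5 | 0.15 × 0.5 = 0.075 | 17% |
| 10% | 1.0 | 0.10 × 1.0 = 0.100 | 23% |
| 15% | 1.0 | 0.15 × 1.0 = 0.150 | 35% |

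**6. Exclusion in both arms at different rates (assumed inputs).** Take 100 randomised per arm, no true effect, 20% excluded from the app arm and 10% from control, with excluded patients 0.5 SD below their own arm's overall mean. Then D = 0.5 / (1 − m), and the bias is 0.20 × 0.5/0.80 − 0.10 × 0.5/0.90 = 0.125 − 0.056 = 0.069 SD, or 16% of 0.43. With 80 and 90 analysed, the standard error is √(1/80 + 1/90) = 0.154, the shift is 0.45 standard errors, and the two-sided type I error is 7.4%. Swapping the two rates gives −0.069 SD, so the sign depends on which arm loses more.

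**The case against.** The strongest reply is that this is a risk and not a shown bias. That stands: the article gives no exclusion rate by arm and nothing on how excluded patients differ. The filter is also milder than a completers' rule, since only patients without step data from day 30 are lost, probably a part of the planned 15%.

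A reader might infer several stronger things that the article does not support:

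- **That patients who stop the app are removed while controls have nothing to stop.** The on-treatment condition is not defined as app use. It is attached to the primary endpoint, which is steps on the monitor. Both arms wear the monitor, so a control patient can also stop wearing it.
- **That PAM-13, knee pain and mood are cut to the same set.** The article lists these as patient-reported or tertiary outcomes. Whether they count as efficacy outcomes is unclear; for the 6-minute walk it is explicit.
- **That the bias favours the app.** If the least mobile controls stop recording, the bias runs against it.
- **That the stated limitation on blinding already shows the problem.** The remark that "the investigators are not blinded to the intervention" concerns the delivery of other care, not step recording.

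It can also be said that missing-data methods belong in an analysis plan that is not shown. That is fair for the choice of model and for sensitivity analyses. It does not answer the main point, because the article itself fixes the efficacy population.

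**Conclusion.** The point holds as a risk of selection bias of unknown sign and size. The efficacy set is defined by an event after randomisation that the open-label, arm-specific feedback can influence, and the article describes no efficacy analysis of all randomised patients.

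The bias is zero when exclusion rates and mechanisms match across arms. The illustrative 12-35% of the detectable difference assumes that exclusions fall in one arm only and that those patients differ by 0.5-1 SD from those retained. None of these inputs comes from the article. The 0.43 SD yardstick assumes 85 evaluable patients per arm. To say that randomisation has already been lost would go further than the text allows. Separately, and without any such assumption, the rule drops valid 6-minute walk results from patients who lack step data.

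**What to change.** - Define the primary analysis as all randomised patients in their assigned arm, using all recorded post-baseline steps whether or not the app is in use. Remove the on-treatment and day-30 conditions.
- Impute patients with no post-baseline steps, with a control-based sensitivity analysis.
- State how early recordings inform the day-90 comparison. A repeated-measures model on weekly mean steps is one option, not a requirement.
- Analyse the 6-minute walk in all randomised patients in whom it was observed.
- Report the number excluded by arm, and keep the present modified intent-to-treat set as a sensitivity analysis.

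**Cost.** No new data are needed, but there is extra programming. Results for patients with no post-baseline steps will rest on missing-data assumptions that cannot be tested. The article's Discussion reports that enrolment is complete, so the change must be documented and made before comparative data are examined.

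### The single stated ANCOVA adjusts for baseline steps only; this suits the step endpoints but gives up precision on the other continuous outcomes, whose own baselines could be covariates at no cost

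*Protocol article*

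**What the plan says.** The second paragraph of Data Analysis (Protocol article) opens with a statement about efficacy outcomes in the plural: "Efficacy outcomes will be analyzed in the modified intent-to-treat population". The next sentence gives the only comparative model in the article, an ANCOVA "with baseline mean steps per day as covariate and treatment and pooled site as class variables will be used to compare between-group outcomes". No other continuous covariate is named anywhere. Satisfaction surveys are only summarised, so they fall outside this point.

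Study Outcomes defines the endpoints in two ways:

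- **Changes.** The primary endpoint is a change in steps: "The primary study endpoint is the difference in the change in mobility (assessed by steps per day) between groups at the end of 90 days". Physical function is "assessed by the change from baseline in the 6-minute walk test (distance and pain" on a numeric rating scale. PAM-13 (in the secondary objectives) and weight are also changes from baseline.
- **Final-visit values.** Two tertiary endpoints are levels: "target knee pain with walking and at rest, as measured by the 11-point numeric rating scale at final visit", and "mood at final visit (as measured by the VAMS".

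Patient Eligibility Criteria and Study Design has baseline pain assessed at screening. At the return visit, before randomisation, it has baseline activity, VAMS mood "and a baseline 6-minute walk test".

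**The concern.** For most continuous outcomes the best single predictor of the final value is the same measure at baseline. Baseline steps fills that role for steps per day. It has no such claim for walking distance, knee pain, mood, activation score or weight. If the sentence is followed literally, the comparisons of final-visit pain and mood ignore the pain and mood data taken at the start, and the change-score comparisons forgo the regression adjustment that ANCOVA offers.

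What is at stake is efficiency: wider confidence intervals and lower power on secondary and tertiary endpoints. Chance baseline imbalance carried into the estimate is the same loss seen from another side, so it should not be counted twice.

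**Working it through.** **The plan's own figure.** Data Analysis states 200 participants, 15% attrition, two-sided 5% and 80% power. 200 × 0.85 = 170 evaluable, or 85 per arm, so N and attrition agree. The power cannot be reproduced because no SD is given. The implied standardised effect is (1.960 + 0.842) × √(2/85) = 0.43. None of this depends on the covariate used for non-step outcomes.

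**Inputs for the precision check.** From the documents: 1:1 allocation, 85 evaluable per arm, and the definition of each endpoint as change or final value. Assumed: r, the correlation between an outcome's baseline and final value; r0, the correlation between baseline steps and that outcome's own baseline; equal variance σ² at both times; and steps related to the final value only through the own baseline.

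**Residual variance per patient, in units of σ², with r0 = 0:**

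- final value without own baseline: 1
- change score without own baseline as covariate: 2(1 − r)
- own-baseline ANCOVA, for either form: 1 − r²

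| r | final | change | own-baseline ANCOVA | cut vs final | cut vs change |
|---|---|---|---|---|---|
| 0.5 | 1 | 1.00 | 0.75 | 25% | 25% |
| 0.7 | 1 | 0.60 | 0.51 | 49% | 15% |
| 0.8 | 1 | 0.40 | 0.36 | 64% | 10% |

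Outside this range, r = 0.3 gives 1 − 0.91 = 9% for final values and 1 − 0.91/1.40 = 35% for changes. At r = 0.9 the figures are 1 − 0.19 = 81% and 1 − 0.19/0.20 = 5%. The two endpoint types move in opposite directions as r rises.

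**Allowing baseline steps to carry some information.** The variance with steps only, relative to steps plus own baseline, is

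- final value: (1 − r0²r²)/(1 − r²)
- change: [2(1 − r) − r0²(1 − r)²]/(1 − r²)

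With r0 = 0.5:

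- r = 0.5: both ratios are 0.9375/0.75 = 1.25, a cut of 20%.
- r = 0.8: final 0.84/0.36 = 2.33, a cut of 57%; change 0.39/0.36 = 1.08, a cut of 8%.

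**In terms of power.** Take an effect for which own-baseline ANCOVA has 80% power at 85 per arm, with r0 from 0 to 0.5. Steps-only power is then:

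- r = 0.5: 0.68 to 0.71 for both types
- r = 0.8: 0.39 to 0.45 for final values and 0.76 to 0.77 for change scores

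**Simulation check** (85 per arm, r0 = 0.3, no treatment effect, 3,000 replicates). Variance ratios were 1.30 (r = 0.5) and 2.64 (r = 0.8) for final values, and 1.29 and 1.10 for change scores. The formulas give 1.30, 2.62, 1.30 and 1.10. The mean estimated contrast stayed within 0.006 SD of zero under both models, so neither is biased.

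**The case against.** The strongest reply is that the sentence does not say it covers every outcome. The sample-size paragraph before it concerns steps only, the analysis set is defined through the primary endpoint, and the article condenses a fuller protocol that may assign each endpoint its own baseline. A reader could fairly take the sentence as the model for the step endpoints. This stands as a caution: a universal prescription is an inference. It does not remove the point. The sentence follows one about efficacy outcomes in the plural, carries no restriction to steps, and names a covariate rather than staying silent. If a fuller plan already uses own baselines, the article's sentence misdescribes it.

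Four stronger readings are tempting and are not supported:

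- **Walk distance goes unadjusted for its baseline.** It does not. Walk distance and walk-test pain are change scores, as are PAM-13 and weight, so the baseline enters by subtraction. Only regression adjustment is missing, and that loss is small when r is high.
- **The main secondary endpoint is affected.** The 6-minute walk is listed first, but the article gives no ranking among secondary endpoints.
- **The treatment effect would be biased.** Under randomisation it is not; only precision suffers.
- **Every affected outcome has a recorded baseline.** Baseline pain is assessed, and the eligibility criterion concerns pain while walking. A baseline for pain at rest is not explicit.

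The reply that the size rests on assumed correlations also stands. No correlation is given, and nothing shows how strongly baseline steps relates to these outcomes.

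**Conclusion.** The point holds as one of efficiency. As written, the only continuous covariate is baseline steps. That is appropriate for the primary endpoint and for percent change in steps, and inefficient elsewhere. The loss is clearest for final-visit knee pain and VAMS mood, both tertiary, where the own baseline would not be used at all. It is more modest for the change-score endpoints if r is high.

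Over assumed correlations of 0.5 to 0.8, with little correlation with steps, the avoidable residual variance is about 25% to 64% for final-value outcomes and about 25% falling to 10% for change scores. If baseline steps correlates 0.5 with the own baseline, these become 20% to 57% and 20% to 8%. The direction is the same for every correlation tried, from 0.3 to 0.9; the size depends on figures the documents do not give. Validity, the primary analysis and N = 200 are not in question. This is a free improvement, not a defect that threatens the trial's conclusion.

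**What to change.** Replace the single-covariate sentence with one that separates the endpoints. Step endpoints: ANCOVA with baseline mean steps per day, treatment and pooled site. Each other continuous endpoint: ANCOVA with that endpoint's own baseline value where collected, plus treatment and pooled site. That means baseline walk distance for walk distance, baseline walk-test pain for walk-test pain, baseline knee pain for knee pain, and baseline VAMS score for mood, with PAM-13 and weight handled likewise. Baseline steps may be kept as an additional covariate if wished. For pain at rest, say whether a baseline exists and, if not, which covariate is used.

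The cost is a sentence or two. Baseline pain, mood and walk test are already scheduled, so no new data are needed for them. The Discussion says enrolment is complete. That does not prevent the change, provided it is fixed and dated before outcome data are analysed. If a fuller plan already specifies own baselines, the only action is to make the article's wording agree with it.
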